**Figure 2 fig2:**
[figure not shown]
Recruitment and randomization of the clinical trial. AHI, apnea-hypopnea index; OSA, obstructive sleep apnea.

The sample will be selected by non-probabilistic sampling. Participants will be recruited through partnerships with public and private institutions in Grande Florianopolis, Santa Catarina, Brazil. Additionally, the study will be promoted through healthcare services, elderly community groups, local media (radio and newspapers) and, if necessary, leafleting in neighborhoods near the university and during technical-scientific events.

### Sample size

2.3

To determine the minimum number of participants required for the interventions, the sample size was calculated using the GPower 3.1 software. Using repeated measures ANOVA (within-subjects and between-subjects interaction) and assuming a significance level (α) of 0.05, power (β) of 0.95, and effect size of 0.35 (da Silva et al., 2022), the minimum sample size is 30 individuals. This number will be increased by 20% to account for potential sample losses, resulting in a minimum sample size of 36 participants divided into two groups: – the exercise group (EG) and the control group (CG), each consisting of 18 subjects. Losses after randomization will be included in the intention-to-treat analysis but not in the analysis of the protocol.

### Eligibility outcomes

2.4

#### Obstructive sleep apnea

2.4.1

To assess the risk of OSA in older adults, the STOP-BANG questionnaire (Chung et al., 2012) will be administered, which is designed to identify individuals at a higher risk of developing apnea. This screening instrument consists of eight questions that evaluate risk factors for OSA, with the responses being categorized as “yes” or “no.” The score ranges from 0 to 8 and scores ≥3 have shown high sensitivity in detecting moderate to severe OSA (Chung et al., 2012).

After the first assessment, participants classified as being at higher risk for OSA will undergo type III home polysomnography (HPSG) (Philips Respironics Alice NightOne). HPSG consists of the concurrent monitoring of sleep and respiration using thoracic and abdominal belts, an oximeter (to capture oxygen saturation and heart rate), and a nasal cannula (to monitor airflow and snoring), as well as the recording of body position during sleep (Jordan et al., 2014; Lee and Sundar, 2021). The following data will be obtained: AHI, ODI, minimum and mean oxyhemoglobin saturation (SaO2), sleep efficiency, sleep latency, and the type of respiratory event. Only individuals exhibiting an AHI ≥15 events per hour will be eligible for participation in the study.

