### Participants

2.2

The following inclusion criteria will be applied to select the participants in this randomized clinical trial (Figure 2): age between 60 and 79 years; both genders; moderate to severe OSA with an AHI > 15 events per hour, and no history of previous or ongoing treatment for OSA. Older adults who have engaged in regular exercise in the last six months and those with contraindications (cardiovascular, respiratory, musculoskeletal, or neurological) to exercise will be excluded. Participants who do not adhere to the interventions at a rate ≥ 85% will also be excluded from the study.

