## Discussion

3

This study aims to investigate the impact of a combined exercise program and sleep education on the severity and symptoms associated with OSA among older adults. The hypothesis posits that the combination of resistance and aerobic exercises, along with sleep education, will effectively reduce both the severity and the symptoms of OSA in older adults compared to the control group. This protocol is based on previous research demonstrating the potential of combined physical exercise to mitigate OSA severity in middle-aged adults (Kline et al., 2011; Desplan et al., 2014; Bughin et al., 2020).

The strengths of this study include the direct assessment of OSA using HPSG and the analysis of various symptoms associated with the disorder such as sleep quality and efficiency, as well as the measurement of anthropometric variables. The use of validated instruments increases the validity and reliability of the results. Participant recruitment will be broad but specific, with the inclusion criteria being based on previous studies and considering the specificity of OSA. Furthermore, the ecological validity of the study is considered, especially in relation to the exercise intervention, enabling its application in clinical practice. These strengths provide a solid framework and will thus increase the internal validity and clinical relevance of the study, which will contribute to scientific knowledge and improve the quality of life of older people with OSA.

The present study is of great importance for the scientific advancement in this field since it aims to investigate whether the positive effects of combined exercise on OSA are also observed in older people. If the study results demonstrate significant improvements in sleep parameters and OSA severity after the combined exercise program, this may indicate an effective non-pharmacological intervention for treating these conditions in older adults. This discovery would be of great clinical relevance by adding a non-pharmacological therapeutic option to the treatment of OSA in this population, which could be used as an adjunct to existing approaches. Moreover, effective intervention for managing sleep apnea in older adults may result in substantial savings in public health costs by preventing complications caused by OSA and reducing the need for expensive medical treatments.

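### Sleep efficiency and sleep latency are to come from a home recorder whose listed sensors do not detect sleep, and the hourly AHI and ODI have no stated denominator

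*Protocol article*

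**What the plan says.** Section 2.4.1 of the protocol article states that "participants classified as being at higher risk for OSA will undergo type III home polysomnography (HPSG) (Philips Respironics Alice NightOne"). It describes the recording as covering sleep as well as breathing, and lists the sensors as "thoracic and abdominal belts, an oximeter (to capture oxygen saturation and heart rate), and a nasal cannula (to monitor airflow and snoring"). The only further channel it mentions is body position. It then states: "The following data will be obtained: AHI, ODI, minimum and mean oxyhemoglobin saturation (SaO2), sleep efficiency, sleep latency, and the type of respiratory event".

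The abstract (Methods) names sleep efficiency and sleep latency among the OSA-related outcomes, next to AHI and ODI. Elsewhere the two appear only as self-reported components of the PSQI (section 2.5.1).

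AHI is given throughout simply as a rate per hour. It decides entry (sections 2.2 and 2.4.1), and its change enters the correlation analysis (section 2.10). OSA severity defines a randomisation stratum (section 2.7) and is part of the study aim (section 1). The entry limit is "moderate to severe OSA with an AHI > 15 events per hour" in section 2.2, and the abstract agrees with that. Section 2.4.1 has "Only individuals exhibiting an AHI ≥15 events per hour will be eligible for participation in the study".

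**The concern.** Sleep latency needs the time of sleep onset. Sleep efficiency needs total sleep time as well as time in bed. Belts, oximetry, nasal airflow and body position supply neither, and the article describes no brain-activity, eye-movement or muscle-tone channel, no actigraphy, no diary and no sleep-time algorithm. Two outcomes would then be reported without a measured basis.

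The same gap reaches the severity index. Without measured sleep time, a rate per hour must use recording time or some substitute that is not described. A recording-time rate depends on how much of the recording is spent asleep. The introduction cites evidence that exercise improves sleep efficiency, so this fraction could change more in the exercise arm than in the control arm. Randomisation does not remove an error that the treatment itself produces.

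**Working it through.** The plan gives no figure on this point, so there is none to reproduce. The check has three parts.

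**1. Variables against sensors (section 2.4.1)**

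| Variable promised | Input needed | Listed sensor that supplies it |
|---|---|---|
| Saturation, ODI event count | oximetry | oximeter |
| Respiratory event count and type | airflow, effort, saturation | cannula, belts, oximeter |
| Sleep latency | time of sleep onset | none |
| Sleep efficiency | total sleep time / time in bed | none for the numerator |
| Denominator of AHI and ODI | hours | recording hours only; sleep hours not available |

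**2. What a recording-time denominator would do**

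If all events occur in sleep, then

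index per recording hour = index per sleep hour × s, where s = sleep time / recording time.

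The document gives no value of s, so every value below is an assumption.

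- At entry: a recorded 15 per hour corresponds to 15 / 0.85 = 17.6 events per sleep hour when s = 0.85, and to 15 / 0.70 = 21.4 when s = 0.70.
- Over time: assume a true fall of 20%, from 30 to 24 per sleep hour. The recorded change is 0.80 × (s after / s before) − 1.

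| s before | s after | Recorded index | Recorded change |
|---|---|---|---|
| 0.75 | 0.75 | 22.5 to 18.0 | −20.0% |
| 0.75 | 0.80 | 22.5 to 19.2 | −14.7% |
| 0.75 | 0.85 | 22.5 to 20.4 | −9.3% |
| 0.70 | 0.85 | 21.0 to 20.4 | −2.9% |

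- Between arms: suppose s changes by the same factor r in both arms and controls have no true change. The ratio of the arms' relative changes is (0.80 × r) / (1.00 × r) = 0.80, as without any change in s. The relative contrast is distorted only if s changes differently in the two arms.

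**3. Entry cut-off**

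The abstract and section 2.2 require more than 15; section 2.4.1 admits 15 or more. The rules disagree only for a value of exactly 15. This is independent of the sensor question.

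**The case against.** The sensor sentence can be read as a general description of the method, with outside references, and not as the full channel list of the named device. The full protocol may name a further channel or a software estimate of sleep. That is possible, and it is why the fix allows for one to be named. It does not remove the conflict: the article lists specific sensors and then promises variables that none of them supplies.

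A reader might infer that AHI is in fact computed per recording hour. The article does not say so. A trimmed or estimated sleep time is also conceivable. What stands is that the denominator is unstated and cannot be measured sleep on these sensors.

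A reader might also infer a definite loss of effect, for example over a third if AHI truly falls from 30 to 24 while efficiency rises from 75% to 82%. None of those values is in the document. Both arms receive sleep education (section 2.8), and the loss requires a between-arm difference in sleep change. If that difference favours the exercise arm, the error is conservative.

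The strengths paragraph in the Discussion, "the analysis of various symptoms associated with the disorder such as sleep quality and efficiency", might be read as crediting the recorder with efficiency. It lists this as an item separate from the recorder, and the PSQI has a habitual-efficiency component, so the sentence can be true as it stands.

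Finally, the outcomes under section 2.5 are the PSQI and ESS, and section 2.10 names AHI and ODI only for the correlations. This limits the consequence. But OSA severity is in the aim and hypothesis, and AHI governs entry.

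**Conclusion.** The contradiction within section 2.4.1 holds: on the listed sensors, sleep efficiency and sleep latency have no measured input, and AHI and ODI cannot be rates per hour of measured sleep. This needs no assumption beyond taking the sensor list as written.

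The effect on the severity index is conditional. It needs a recording-time denominator and a larger gain in sleep fraction in the exercise arm; the index would then understate a benefit. The table's range, from the full 20% down to about 3%, is an illustration under assumed sleep fractions and not an estimate for this trial.

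The cut-off mismatch is real but minor, and it is a separate wording matter.

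**What to change.** 1. Remove sleep efficiency and sleep latency from the recorder outcomes in section 2.4.1 and the abstract, unless a recorded channel or validated algorithm that measures sleep is named.
2. Report any PSQI latency or efficiency component only as self-report and as part of the PSQI. These components already count towards the global score, and participants are not blinded, so they are no objective substitute.
3. Define the index as events per hour of valid recording time (a respiratory event index), with one rule at entry, stratification, baseline and week 12. This does not remove its dependence on sleep fraction, but it makes the meaning of the index plain.
4. Reconcile the entry cut-off across the abstract and sections 2.2 and 2.4.1.

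The strengths paragraph needs no change. The work is rewording; the real cost is giving up two listed objective outcomes if no sleep measurement can be named.

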#### Clinical restrictions and prior or current regular exercise

2.4.2

Participants will be asked questions regarding their history of cardiovascular, respiratory, musculoskeletal, and neurological conditions to determine any clinical restrictions for participation in exercise. These questions developed by the research team are aimed at identifying potential health issues that may restrict the participant from participating in this clinical trial. The following two questions will be used to determine whether the participant currently exercises or has engaged in regular exercise in the last six months, which will also be used as inclusion criteria: (a) “Do you currently exercise?” and (b) “Have you regular exercise in the last six months?”

### Primary outcomes

2.5

#### Sleep quality

2.5.1

The Pittsburgh Sleep Quality Index (PSQI) (Buysse et al., 1989) will be used to evaluate sleep quality. The PSQI has been validated for use in Brazil (Bertolazi et al., 2011), showing high internal consistency (Cronbach’s α = 0.82). The questionnaire consists of 19 items that assess various sleep-related issues over the past month. The questions are divided into seven components and a score ranging from 0 to 3 is assigned to each component. These components include sleep quality, sleep duration, sleep latency, habitual sleep efficiency, sleep disturbances, medication use, and daytime dysfunction. The sum of scores for each component provides a global score ranging from 0 to 21, with higher scores reflecting poorer sleep quality. A score above 5 indicates poor quality (Buysse et al., 1989).

#### Daytime sleepiness

2.5.2

Daytime sleepiness will be assessed with the Epworth Sleepiness Scale (ESS) (Johns, 1991). The instrument has been validated for use in Brazil, with a reliability coefficient of 0.83 (Bertolazi et al., 2009). The ESS is aimed at evaluating the likelihood of dozing off in eight situations known to induce sleepiness. Respondents are required to indicate the probability of falling asleep in each situation, which ranges from “would never doze” (0) to “high chance of dozing” (3). The overall score ranges from 0 to 24 and a score above 10 suggests a diagnosis of excessive daytime sleepiness (Johns, 1991).

### Secondary outcomes

2.6

#### Physical activity and sedentary behavior

2.6.1

The International Physical Activity Questionnaire (IPAQ) adapted for older adults will be used to investigate physical activity. This instrument has been validated for use in Brazilian older adults (Mazo and Benedetti, 2010), showing good reproducibility (Benedetti et al., 2004). The IPAQ estimates the weekly energy expenditure from physical activity across various domains. These domains include physical activity at work, physical activity during transportation, household physical activity, recreational, sports and exercise-related physical activity, and sedentary behavior.

The adapted version consists of 15 questions that evaluate moderate to vigorous physical activity; these activities should be performed for at least 10 consecutive minutes to be considered. In the current study, only sections four (recreational, sports and exercise-related physical activity) and five (sitting time) of the IPAQ (Mazo and Benedetti, 2010) will be administered and the time in minutes/week of moderate and/or vigorous physical activity will be calculated to classify the sample as active (≥150 min/week) or insufficiently active (<150 min/week).

#### Physical fitness

2.6.2

The physical fitness of the participants will be assessed using the Senior Fitness Test battery (Rikli and Jones, 1999), which evaluates the physiological capacity of older adults to perform habitual activities of daily living. The battery consists of the following tests: chair stand to estimate lower limb strength; arm curl to assess upper limb strength; chair sit-and-reach to measure lower limb flexibility; back scratch to test upper limb flexibility; 8-foot up-and-go to analyze coordination, dynamic balance, and agility, and 6-min walk to evaluate aerobic endurance.

This battery will be used because of its specificity and validation in the elderly population (Rikli and Jones, 1999), its ease of application, and operational cost-effectiveness. In addition, this instrument has been used across different countries, including Brazil (Silva et al., 2019; Gonçalves et al., 2021). The results will be analyzed based on the difference (Δ) between the values obtained by the participants in the tests before and after the interventions.

#### Aerobic capacity

2.6.3

Aerobic capacity will be assessed based on maximal oxygen consumption (VO_2_max). VO_2_max will be measured directly by an external researcher using a treadmill exercise test according to the modified Bruce protocol (Lerman et al., 1976). The test will be conducted using ergospirometry equipment capable of collecting direct measurements of O_2_ and CO_2_ concentrations, respiratory exchange ratio, heart rate, and ambient temperature and pressure in real-time. Pre-test instructions will be provided to the participants in accordance with the guidelines of the American Heart Association (Fletcher et al., 2013). For safety reasons, all tests will be supervised by a cardiology professional. Exhaustion will be defined when at least one of the following criteria is met: Borg rating of perceived exertion ≥18 out of 20 associated with a respiratory exchange ratio exceeding 1.10, and/or reaching a peak heart rate ≥ 85% of the predicted maximum heart rate, and/or achieving a point of stabilization in oxygen uptake (Vecchiato et al., 2022).

#### Cognitive status

2.6.4

The Mini-Mental State Examination (MMSE) will be used to evaluate the cognitive status of the participants. The MMSE was developed by Folstein et al. (1975) and was validated for use in Brazil (Bertolucci et al., 1994). The instrument generates a maximum final score of 30 points, corresponding to high cognitive capacity. The cutoff values to determine preserved cognitive status take into account the educational level (Brucki et al., 2003).

#### Body composition

2.6.5

Anthropometric and body composition measurements will be carried out to examine various outcomes. These measurements will be used to determine possible correlations with changes in the primary outcomes of OSA after the intervention. Body weight will be measured with a G-Life^®^ Millenium digital scale (silver model CA6000). Height will be measured with a Cardiomed^®^ stadiometer (height limit of 2.16 m) from the feet to the highest point of the head. The body mass index (BMI) will be calculated from the body weight and height using the formula: BMI (kg/m^2^) = body weight (kg)/height^2^ (m). Neck circumference (NC) will be measured with a Cescorf^®^ measuring tape immediately above the thyroid cartilage.

Body composition will also be evaluated by whole-body dual-energy X-ray absorptiometry (DXA) using a Hologic system (Discovery Wi Fan-Beam, Bedford, Massachusetts, United States). The equipment will be calibrated daily and weekly according to the manufacturer’s recommendations. The same lab technician will position the participant for each scan, perform the scans, and analyze the data according to the operator’s manual using the standard analysis protocol. DXA provides data on bone mineral content (g), bone mineral density (g/cm^2^), lean mass (kg), and fat mass (kg).

#### Quality of life

2.6.6

Quality of life will be analyzed using the Quebec Sleep Questionnaire (Lacasse et al., 2004), an instrument specifically designed to assess the quality of life of individuals with OSA. The questionnaire has been translated and adapted for use in Brazil (de Melo et al., 2017) and comprises 32 questions that evaluate the impact of apnea across five distinct domains: daytime sleepiness, daytime symptoms, nighttime symptoms, emotions, and social interactions. Each domain consists of four to 10 items, each scored on a Likert scale ranging from 1 to 7. The results will be presented individually for each domain considering the mean score obtained for each domain (Lacasse et al., 2004).

#### Treatment satisfaction

2.6.7

To evaluate satisfaction with the treatments, participants will complete a brief questionnaire based on the study by Kline et al. (2011), which assesses the expected changes in the severity of OSA, sleep quality, daytime sleepiness, mood, and overall health. Responses will be rated on a Likert scale, where 1 = much worse and 5 = much better. Additionally, participants will be asked about their overall treatment satisfaction using a Likert scale, where 1 = very dissatisfied and 2 = very satisfied.

### Data collection

2.7

Before the recruitment process, participants will receive an explanation of the objectives and assessment procedures of the study. Upon agreeing to participate, the older adults will read and sign the informed consent form. Participants will then respond to the questionnaires and undergo HPSG to determine their eligibility for the study. After confirmation of their eligibility, older adults will complete the remaining questionnaires and undergo the remaining tests. Assessments regarding HPSG will be conducted by an assessor blind to treatment allocation. Because of the inherent characteristics of the intervention, it is not possible to maintain blinding for either the participants or the researcher regarding allocation. However, both are strongly advised against revealing the allocation status of participants during follow-up assessments.

Next, participants will be randomized to two groups: the exercise group (EG) and the control group (CG). To ensure similarity in participant characteristics within the groups, stratified randomization will be conducted to control the covariates sex (2 levels: male and female) and OSA severity (2 levels: moderate and severe). For this purpose, an external researcher will generate a computerized sequence of random numbers to determine the 1:1 allocation to either EG or CG based on the order of participant recruitment. The specific schedules for instrument administration and the data collection procedure are outlined in Figure 3.

**Figure 3 fig3:**
[figure not shown]
Clinical trial design. HPSG, Home Polysomnography; PSQI, Pittsburgh Sleep Quality Index; ESS, Epworth Sleepiness Scale; IPAQ, International Physical Activity Questionnaire; SFT, Senior Fitness Test; MMSE, Mini-Mental State Examination.

### Experimental design

2.8

As previously mentioned, participants will be allocated to either EG or CG. Participants randomized to EG will undergo a 12-week intervention, three times per week, totaling 36 sessions. Each training session will last approximately 60 min and will be organized as follows: warm-up (5 min), training (50–60 min), and cool-down (5 min). Training intensities will be progressively adjusted throughout the weeks according to the principle of overload.

The intervention will consist of a training program that combines aerobic and resistance exercises within the same session. This approach is based on other studies that have applied similar training programs to adults with OSA (Kline et al., 2011; Desplan et al., 2014; Bughin et al., 2020). The combined exercise approach is also in line with the physical activity recommendations for Brazilian older adults, which suggest the prescription of both types of exercise (de Coelho-Ravagnani et al., 2021). Each training session will start with a warm-up (5 min), followed by aerobic exercise (20 min) and resistance exercises (30 to 40 min), and concluding with a cool-down (5 min).

The aerobic training protocol will be conducted on a treadmill or stationary bicycle, with intensity corresponding to the anaerobic threshold determined based on the ventilatory thresholds established in the stress test. Pre-test instructions will be provided to participants in accordance with the recommendations of the American Heart Association (Fletcher et al., 2013). Heart rate will be monitored during the sessions using a Polar heart rate monitor.

The resistance exercise protocol will consist of exercises for the legs, arms, chest, back, and abdomen. All exercises will comprise three sets, with a rest interval of 90 s. Additionally, the intervention will be divided into three phases: familiarization, load determination, and training. The familiarization phase will involve learning the proper range of motion, breathing, and rhythm for each exercise. Participants will be instructed to inhale during the eccentric phase and to exhale during the concentric phase of the exercise, performing repetitions at a tempo of two seconds for each phase of the movement.

Loads will be determined using the maximum repetition (RM) test to define loads within the training target zone, which will be set at 10 RM in this study. This load determination is based on various studies (Jambassi Filho et al., 2011; Gurjão et al., 2012; Virtuoso et al., 2019). Participants will be instructed to perform as many repetitions as possible with a load subjectively chosen by the researcher (trial and error). During this determination process, a maximum of two attempts will be made for load definition, with a recovery interval of 3 to 5 min. If a participant completes more than 12 repetitions, 1 kg will be added for every two additional repetitions. If the number of repetitions falls below 8 RM, the load will be adjusted through trial and error. To ensure accuracy in load definition and to assess reproducibility, the tests will be repeated after a minimum interval of 48 h. Following the load determination, participants will start the resistance exercises as part of the intervention.

In addition to the exercise, participants in EG will also receive sleep education, which will include information on sleep hygiene and on the pathophysiology, risk factors, and treatments of OSA. Sleep education will also be administered to participants randomized to CG so that they would adhere to the recommendations of the American Academy of Sleep Medicine (AASM) (Epstein et al., 2009). A booklet containing information about sleep hygiene will be provided to CG participants before the start of the intervention. Furthermore, recorded videos on the pathophysiology, risk factors, and treatments for OSA will be sent remotely to the participants. These materials will be systematically distributed over the 12-week period. The participants will also be asked to maintain their normal activities and not to perform exercise. After the research period, CG participants will be referred for appropriate treatment according to medical recommendation.

